### Training

The SLTs in the intervention group will receive training from the research team and will then, in turn, train teaching assistants in schools to deliver the E-PLAYS intervention to the children. Training for SLTs will be kept to the minimum as the aim of this feasibility study is to explore the feasibility of implementing E-PLAYS within the NHS nationally without research team support. Therefore, SLTs will be introduced to the E-PLAYS game and to the manual only. The SLTs will use a training manual with which to train teaching assistants which covers the delivery of E-PLAYS in depth. They will train teaching assistants for around 1 h.

### Quantitative outcome measures

In addition to basic demographic data on age, gender and ethnicity, selected quantitative measures have been chosen for sound psychometric properties (validity, reliability, internal consistency, inter-rater reliability). The specific feasibility outcomes to ascertain recruitment, measure treatment fidelity, test acceptability of both the intervention and of the measures used, and test the feasibility of data collection for language and communication measures, social and mental health measures, generalisation and cost effectiveness for an economic evaluation are given below, with details of the instruments, scales, assessments and interviews to be used:

#### (a) Recruitment measures

A recruitment log will be kept to determine participation, drop-out and completion rates to inform a possible future full-scale trial.

#### (b) Language and communication outcome measures

##### (i) The Children’s Communication Checklist-2, (CCC-2, [43])

The CCC-2 is the most widely used, standardised questionnaire of communication impairment in research and clinical contexts and will be completed by teachers.

##### (ii) Test of Pragmatic Skills, (TPS, [44]).

This is an observational elicitation measure. The tester (RA) engages the child in structured play in which test questions are embedded. The TPS was a sensitive indicator and successful at detecting improvements in communication in our pilot study; it has been standardised on 650+ children by the author. It will be administered by blinded RAs.

##### (iii) Clinical Evaluation of Language Fundamentals-5 (CELF-5, [45]).

We will use one of the subscales; recalling sentences. This sentence repetition assessment is a frequently used measure and is generally regarded as a measure of overall language ability drawing upon a wide range of language processing skills [46]. This will also be administered by blinded RAs.

#### (c) Social behaviour, friendship and mental health measure

##### The Strengths and Difficulties Questionnaire

The Strengths and Difficulties Questionnaire (SDQ) is regarded as the ‘gold standard’ measure and is widely used as a mental health indicator with subscales assessing behavioural, emotional and peer problems. This will be completed by teachers [47].

#### (d) Measure of generalisation to social contexts

##### Dyadic collaborative construction task (Magformers®)

A frequently reported issue with interventions targeting children with SCI is that the skills learned do not generalise to contexts beyond those of the intervention. In order to explore whether communication skills learned through E-PLAYS do in fact generalise to other contexts, children will be video-recorded undertaking a typical classroom collaborative task with a peer. The task we will ask the children to complete involves constructing a Magformers® model following a set of video-recorded instructions; this will take around 10 min. Magformers® are plastic, brightly coloured, magnetised blocks (similar in size to Lego® but different in shape and operation) with which it is possible to construct small models (see magformers.co.uk). All children in intervention and control groups will undertake this task and be recorded; children’s use of different kinds of communication will be observed and coded from the video-recording. The Magformers® construction task will be facilitated and video-recorded by blinded RAs who will also undertake coding of the transcripts from the video-recordings.

#### (e) Health-economic measures

##### (i) Bespoke Questionnaire

A bespoke questionnaire designed by the team’s health economist based on previous work in studies with children will measure the child’s health services-use (parent-completed, non-blinded).

##### (ii) EQ-5D-Y [48], PedsQL [49]

Health utility: both the parent proxy EQ-5D-Y [48] and the parent proxy PedsQL [49] will provide measures of health-related utility.

For the feasibility study, we will not undertake a full economic evaluation; we will assess intervention and trial costs only. We will estimate research and implementation costs of undertaking a full trial.

### Data collection points for outcome measures

Data collection for the TPS, CCC-2, CELF-5 Recalling Sentences subscale, SDQ and Magformers® construction task will take place at baseline, 15–20 weeks and 35–40 weeks post-randomisation. These time points are equivalent to baseline, immediate post-intervention and 3-month follow-up for the intervention group. All health economic measures will be collected at 35–40 weeks post-randomisation (see Fig. 1. SPIRIT figure for E-PLAYS trial for data collection timings). Data will be collected at three times points from teachers, parents and the children themselves. As we are working with young children who may tire easily, measures will be collected in two to three short (< 30 min) sessions when necessary.

**Fig. 1 Fig1:**
[figure not shown]
SPIRIT figure for E-PLAYS study

### Process evaluation

As recommended by the Medical Research Council (MRC) guidance for RCTs [50], we will supplement quantitative feasibility testing of E-PLAYS with a qualitative process evaluation which will examine the processes involved in intervention delivery. The processes we will explore are: whether instructions for delivery of E-PLAYS are adequate and clear; whether staff in a real-life NHS and school settings can use E-PLAYS faithfully; how acceptable staff find E-PLAYS; and whether children engage with and enjoy E-PLAYS. By conducting this process evaluation, we hope we may identify any possible influencing mechanisms or unintended negative effects not revealed by quantitative measures. In the event that, for example, we fail to recruit to target, or that fidelity appears compromised, the process evaluation may be illuminative. The process evaluation that forms part of this feasibility trial aims to investigate the following processes linked to implementation:

#### (a) Speech and language therapists’ and teaching assistants’ views

Focus groups with the speech and language therapists and teaching assistants who delivered E-PLAYS will be conducted once delivery is complete, and their views sought on acceptability and ease of use.

#### (b) Children’s views on E-PLAYS

The children’s view will be solicited using the Fun Toolkit [51] (which has been designed to measure children’s views of technology) by an RA immediately after each of two sessions.

#### (c) Fidelity evaluation

(i)On-line recording of the number of intervention sessions completed for each child and their content and duration in minutes will be automatically logged by the E-PLAYS software. For the E-PLAYS computer game, each child will have their own unique login, which will record the number of sessions undertaken, the time that they lasted and which parts of the programme were completed.(ii)E-PLAYS sessions will be observed live by RAs to assess how faithfully teaching assistants actually use it in practice.(iii)We will also explore fidelity issues in the focus groups described above.

#### (d) Training and instructions

Shortly after receiving the instruction pack and manual, SLTs will be asked to complete a short, open-ended questionnaire giving their impressions of its utility and clarity. Teaching assistants will receive a similar questionnaire after they have received the manual and instruction from SLTs (Fig. 2).

**Fig. 2 Fig2:**
[figure not shown]
E-PLAYS study flowchart

## Analysis

### Recruitment data analysis

The number of children recruited and the rate of attrition will be reported by allocation and in total. The number of E-PLAYS sessions completed and their duration will be summarised descriptively for children in the intervention arm.

### Analysis of outcome measures

A detailed analysis plan will be produced prior to the final analysis and will be reviewed by the independent trial steering committee. Analyses will follow intention to treat principles, with all data analysed as randomised. Analyses will be entirely descriptive with scores on the TPS, CCC-2, CELF-5 Recalling Sentences Subscale and Magformers® construction task presented unadjusted at each time point.

For the Magformers® construction task, video-recordings will be professionally transcribed and video-coding will comprise observation and categorisation of communicative (e.g. questions, directives, clarifications) and affective (e.g. positive and negative behaviours) items. The coding system is based on micro-analytic theory [52, 53] and was developed by the team specifically to analyse children’s collaborative interaction and has been shown in our studies to successfully detect changes in talk [29, 39, 54, 55]. The coding system incorporates elements from research into collaborative learning, conversation analysis and language impairment [29, 39, 53–60]. Video interaction will be coded by blinded RAs trained to fidelity by the Chief Investigator who has used this coding system extensively. RAs will train by watching and practice-coding training videos until they reach inter-rater reliability with these previously coded video-recordings. Areas of disagreement with the training videos will be discussed and explained by the Chief Investigator. Inter-rater reliability will further be tested between all RAs taking part in the study using a sample of 15% of all video-recordings.

The analysis of all measures will not be concerned with the effectiveness of the study intervention, but instead will seek to inform the feasibility objectives. In particular, this data will be used to characterise the groups at baseline, assess the proportion of analysable data at follow up and provide estimates of key population parameters, all of which will inform the design of a future full scale trial. The analysis of the health economic data will be principally concerned with the completeness and quality of this data. This will be reported together with a calculated estimate of the costs of running E-PLAYS within the NHS and schools and costs of a possible future full-scale RCT.

### Process evaluation analysis

#### (a) Speech and language therapists’ and teaching assistants’ views

The focus groups (a) will last around 1 h and will be audio-recorded and subsequently professionally transcribed. Nvivo 9 software will be used to aid a thematic analysis which will follow the guidelines of Braun and Clarke [61]:

(1) Becoming familiar with the data, (2) generating initial codes, (3) searching for themes, (4) reviewing themes and (5) defining and naming themes.

#### (b) Children’s views on E-PLAYS

Immediately after participating in sessions, children will be asked to rate their enjoyment and use of E-PLAYS using the Fun Toolkit [51]. The tool is easy to complete and requires no writing. It comprises a ‘Smileyometer’ scale; visual analogue scale with ‘smiley’ faces, ‘Fun Sorter’ (children sort which attributes of the game they like best) and ‘Again Again table’ (children rate which aspects of the game they would like to play again). The tool measures, besides user satisfaction, usability (in software terms) and ease of use. The Fun Toolkit has shown good test-retest reliability in previous research [51]. The Smileyometer, Fun Sorter and Again Again table produce numerical data for scoring; however, they are also designed to stimulate and encourage children to talk about the different aspects of the game and their enjoyment.

#### (c) Fidelity evaluation

##### (i) Number of intervention sessions

Descriptive statistics will be prepared of the number of intervention sessions completed for each child and their content and duration. The possible impact of treatment fidelity and adherence on outcomes will be explored.

##### (ii) Observations

Teaching assistants will be observed by RAs whilst delivering two sessions each to see how they actually deliver E-PLAYS in practice. A crucial aspect of the intervention is the extent to which the instructions in the manual are adhered to. Observers will also record instances of direct verbal feedback and children’s requests for help and comments.

The data from the open-ended questionnaire given to SLTs and teaching assistants will be analysed by coding responses into categories known as a ‘coding frame’ [62]. Given that this is a feasibility study and therefore exploratory in nature, the coding frame will be developed after the data is collected to cover a range of potential responses.

### Sample sizes

#### (a) Quantitative measures

It is not intended that this feasibility study will be powered to detect clinical differences between intervention and treatment as usual groups, this is left for the main trial. We are proposing to collect data on outcomes that will be used to inform a future large-scale trial. Sample sizes of between 24 and 70 have been recommended for feasibility trials to allow for the reliable estimation of a standard deviation for use in future sample size calculations [63, 64]. We therefore aim to recruit 70 children (35 in each group). We anticipate that attrition will be low; this is usually the case for school-based studies with young children, e.g. in our pilot study [39], we lost only one child over a follow-up period of 6 months. However, even with 20% loss to follow-up, we will retain 56 children, which is more than double the recommended minimum sample size. This number will also be sufficient to obtain a reasonably precise estimate of the intra-cluster correlation coefficient for the children grouped by SLT.

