### Randomisation and allocation process

Participating children with SCI will be cluster-randomised at the level of the SLTs. SLTs will be randomised 1:1 to receive either immediate briefing from the research team together with the manual on the E-PLAYS intervention or at to receive this at the end of the trial. Randomisation will take place after SLTs have consented to participate in the study, and have identified and recruited children on their caseloads to participate in the trial but before they receive briefing. Allocation will be via minimisation to ensure balance across the two groups based on the borough of the SLT (there are five boroughs within the district covered by NELFT, each served by a different SLT team) and number of children recruited (dichotomised around the median number of children recruited to form a two level factor). All SLTs will be randomised together as opposed to having a rolling recruitment/randomisation period. The minimisation will be implemented by the trial statistician at the York Trials Unit using MinimPy version 0.3. Once the allocations have been generated, they will be communicated to members of the research team responsible for training the SLTs, while ensuring that the outcome assessors (research assistants) remain blind to these allocations.

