#### (b) Qualitative evaluation

All SLTs and teaching assistants in the intervention group (around seven speech and language therapists and 19 teaching assistants) will receive the open-ended questionnaire. Ten teaching assistants will be observed live delivering E-PLAYS and ten children will give their views using the Fun Toolkit. There will be four focus groups with four to five speech and language therapists or teaching assistants in each group.

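### The sample-size section says the retained children will give a reasonably precise ICC by SLT, but about 14 SLTs with about 4 children each cannot give that precision

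*Protocol article*

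**What the plan says.** The article's section on sample sizes for quantitative measures starts from a rule of thumb: "Sample sizes of between 24 and 70 have been recommended for feasibility trials to allow for the reliable estimation of a standard deviation". It then sets the target, "We therefore aim to recruit 70 children (35 in each group"), and allows for attrition: "even with 20% loss to follow-up, we will retain 56 children, which is more than double the recommended minimum sample size". The next sentence makes the claim at issue: "This number will also be sufficient to obtain a reasonably precise estimate of the intra-cluster correlation coefficient for the children grouped by SLT".

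The number of clusters appears elsewhere. The section on the qualitative evaluation puts "around seven speech and language therapists and 19 teaching assistants" in the intervention group. The section on randomisation makes the SLT the unit of allocation ("Participating children with SCI will be cluster-randomised at the level of the SLTs") and sets the ratio ("SLTs will be randomised 1:1 to receive either immediate briefing from the research team").

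The section on analysis of outcome measures says what the estimates are for. The data are to "provide estimates of key population parameters, all of which will inform the design of a future full scale trial".

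**The concern.** The precision of an ICC is governed by the number of clusters and the number of children per cluster, and a total count of children does not settle it. The claim is expressed only as a number of children. The recommendation cited just before it concerns a standard deviation, so nothing in the section shows that the ICC will be well estimated.

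In a later trial randomised by SLT, the ICC sets the design effect and so the sample size. A planner who took the sentence at face value could enter this study's point estimate as a single value. If that estimate were zero or negative, the full trial would carry no allowance for clustering and would be underpowered. If it were well above the truth, the trial would recruit more children than it needs.

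**Working it through.** **Inputs from the article.** 70 children; 20% loss; about 7 SLTs in the intervention arm; SLTs allocated 1:1.

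**The article's own figures.** 70 × (1 − 0.20) = 56, and 56/24 = 2.33. Both the 56 and the statement that it is more than twice the minimum reproduce. The article gives no figure for ICC precision, so there is none to reproduce.

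**Derived.** Number of SLTs k = 2 × 7 = 14. Retained children per SLT m = 56/14 = 4; with no attrition, m = 70/14 = 5.

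**Assumed.** The ICC r is not in the article and is ranged over 0.05, 0.10 and 0.20. Clusters are taken as equal in size; unequal sizes would generally widen the intervals.

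**Interval.** Exact one-way ANOVA (Searle) limits with arm fitted:
- df1 = k − 2 = 12 and df2 = k(m − 1) = 42
- F0 = [1 + (m − 1)r]/(1 − r)
- each limit = (x − 1)/(x + m − 1), with x = F0/F(0.975) for the lower and x = F0/F(0.025) for the upper
- F(0.975; 12, 42) = 2.271 and F(0.025; 12, 42) = 0.345

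For r = 0.05: F0 = 1.15/0.95 = 1.2105.
- Lower: x = 1.2105/2.271 = 0.533; (0.533 − 1)/(0.533 + 3) = −0.13
- Upper: x = 1.2105/0.3451 = 3.508; (3.508 − 1)/(3.508 + 3) = 0.39

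| ICC estimate | 14 SLTs × 4 | 14 SLTs × 5 (no attrition) |
|---|---|---|
| 0.05 | −0.13 to 0.39 | −0.09 to 0.34 |
| 0.10 | −0.10 to 0.44 | −0.06 to 0.41 |
| 0.20 | −0.03 to 0.55 | 0.01 to 0.52 |

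The half-widths run from about 0.22 (r = 0.05, m = 5) to about 0.29 (r = 0.20, m = 4). Negative limits mean zero in practice.

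**Chance of a zero or negative estimate.** P = P(F(12, 42) ≤ 1/F0). For a true ICC of 0.05 this is P(F ≤ 0.826) = 0.38. For 0.10, F0 = 1.30/0.90 = 1.444 and P(F ≤ 0.692) = 0.25.

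**Error in the other direction.** With 14 × 4, the 97.5th percentile of the estimate is about 0.304 if the true ICC is 0.05 and 0.363 if it is 0.10. The design effect at 5 children per SLT is 1 + 4r.
- True ICC 0.05: (1 + 4 × 0.304)/(1 + 4 × 0.05) = 2.216/1.20 = 1.85
- True ICC 0.10: (1 + 4 × 0.363)/(1 + 4 × 0.10) = 2.452/1.40 = 1.75

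**Sensitivity to the number of SLTs.** With 56 children, an estimate of 0.05 and arm fitted:

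| SLTs | 95% interval |
|---|---|
| 10 | −0.09 to 0.41 |
| 18 | −0.18 to 0.38 |
| 20 | −0.20 to 0.39 |
| 28 | −0.32 to 0.41 |

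The result does not depend on the total being exactly 14.

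**The case against.** The strongest case against the point is that this is a descriptive feasibility study. The sentence affects no allocation, outcome or analysis. The wording is qualitative, and any harm would arise in a later trial that will have its own sample-size section. That bears on how serious the point is, and it is why this is not a must-fix. It does not make the sentence true: estimating parameters for the full trial is a stated purpose of the study, and an analysis plan can add an interval but cannot make it narrower.

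Four stronger readings are tempting, and the article does not support them.

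- *The full trial cannot be sized from this study.* The article says only that the estimates will inform the design. It does not say that this ICC will be the sole input, and it does not rule out external values or a range.
- *Noise alone could more than double the full trial.* This treats a confidence limit as a likely estimate. With 14 × 4, the chance of an estimate that more than doubles the design effect at 5 children per SLT is about 2% for a true ICC of 0, 1% for 0.05 and 0.5% for 0.10.
- *The 24 to 70 rule was misapplied to the ICC.* The article cites it for a standard deviation only, and the ICC sentence follows separately. What stands is that the ICC sentence has no support of its own.
- *The arithmetic is wrong.* It is not; 56 is correct. The fault is an unsupported claim of precision.

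**Conclusion.** The point holds as a correction to the stated precision. On the article's own numbers, the interval at an estimate of 0.05 to 0.10 runs from zero (truncated) to about 0.39 to 0.44, and losing no children lowers the upper end only to about 0.34 to 0.41. An interval that wide cannot tell negligible clustering from heavy clustering. The more likely practical error is to plan with no allowance for clustering (probability 0.38 or 0.25 of a zero or negative estimate at a true ICC of 0.05 or 0.10). Overstatement of the design effect by about 1.75 to 1.85 times is the 97.5th-percentile case.

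The conclusion rests on an assumed ICC, on a total of 14 SLTs derived from an approximate figure for one arm, and on equal cluster sizes. Recruiting 70 children remains justified on the standard-deviation rationale that the article gives.

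**What to change.** Replace the ICC sentence with wording such as: With about 14 SLTs and 4 to 5 children per SLT, the ICC will be estimated imprecisely (95% confidence interval half-width about 0.2 to 0.3 for ICCs of 0.05 to 0.20). It will be reported with its confidence interval and will inform the full trial's sample size only alongside a range of plausible ICCs, not as a single value.

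The cost is one sentence and a less favourable statement of precision. No extra participants, data or analyses beyond the interval are needed, and the recruitment target stays as it is.

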#### (b) Qualitative evaluation

All SLTs and teaching assistants in the intervention group (around seven speech and language therapists and 19 teaching assistants) will receive the open-ended questionnaire. Ten teaching assistants will be observed live delivering E-PLAYS and ten children will give their views using the Fun Toolkit. There will be four focus groups with four to five speech and language therapists or teaching assistants in each group.

